## Abstract

**Background:**

Screening substantially reduces cervical cancer incidence and mortality. More than half of invasive cervical cancers are attributable to infrequent screening or not screening at all. The current study, My Body My Test (MBMT), evaluates the impact of mailed kits for self-collection of samples for human papillomavirus (HPV) testing on completion of cervical cancer screening in low-income, North Carolina women overdue for cervical cancer screening.

**Methods/design:**

The study will enroll at least 510 US women aged 25–64 years who report no Pap test in the last 4 years and no HPV test in the last 6 years. We will randomize participants to an intervention or control arm. The intervention arm will receive kits to self-collect a sample at home and mail it for HPV testing. In both the intervention and control arms, participants will receive assistance in scheduling an appointment for screening in clinic. Study staff will deliver HPV self-collection results by phone and assist in scheduling participants for screening in clinic. The primary outcome is completion of cervical cancer screening. Specifically, completion of screening will be defined as screening in clinic or receipt of negative HPV self-collection results. Women with HPV-negative self-collection results will be considered screening-complete. All other participants will be considered screening-complete if they obtain co-testing or Pap test screening at a study-affiliated institution or other clinic. We will assess whether the self-collection intervention influences participants’ perceived risk of cervical cancer and whether perceived risk mediates the relationship between HPV self-collection results and subsequent screening in clinic. We also will estimate the incremental cost per woman screened of offering at-home HPV self-collection kits with scheduling assistance as compared to offering scheduling assistance alone.

**Discussion:**

If mailed self-collection of samples for HPV testing is an effective strategy for increasing cervical cancer screening among women overdue for screening, this method has the potential to reduce cervical cancer incidence and mortality in medically underserved women at higher risk of developing cervical cancer.

**Trial registration:**

ClinicalTrials.gov NCT02651883, Registered on 11 January 2016.

## Background

More than half of invasive cervical cancers are attributable to screening infrequently or not at all [1]. Almost one fifth of screening-eligible US women report not having completed a Papanicolaou (Pap) test alone within the last 3 years, meaning that they are overdue by current national guidelines [2, 3]. Minority status and low socioeconomic status are associated with lower screening rates, partly due to women’s inability to access preventive care due to resource-related barriers (e.g., poor access to services, inadequate transportation) [4]. Not surprisingly, cervical cancer disproportionately affects low-income and minority populations. Women living below the federal poverty level (FPL) are four times as likely to die from cervical cancer than women living at or above the FPL [5], and black women are more than twice as likely to die from this preventable cancer than white women [6].

Reviews from the Community Preventive Services Task Force (CPSTF) and Cochrane Collaboration recommend client reminders as an effective method for increasing cervical cancer screening in clinic among both regularly screened and under-screened women [7, 8]. Client reminders are sent via mail or telephone to individuals reminding them to attend screening. These reminders often also include information on the benefits of screening, cervical cancer risk, and appointment scheduling assistance [7]. Randomized controlled trials (RCTs) and population-level studies from the USA and Sweden show that offering client reminders with appointment scheduling assistance is effective for increasing screening rates in clinic compared to usual care (i.e., no reminders or appointment scheduling assistance) [9–12]. However, strategies such as mail or phone call reminders have been shown to be less effective or ineffective in increasing cervical cancer screening rates among women who have to take time off work to attend an appointment, have limited transportation options, feel physical discomfort or embarrassment with pelvic examinations, or are not actively participating in a healthcare system [4, 11, 13].

Testing for oncogenic, human papillomavirus (HPV infection), the primary causal agent in cervical cancer, using samples collected by women themselves, yields a similar sensitivity and specificity to HPV testing of physician-collected samples for the detection of high-grade cervical precancerous lesions (cervical intraepithelial neoplasia lesions grade 2 or higher (CIN2+)) [14, 15]. Conducting cervical cancer screening by self-collection of samples at home and return by mail for HPV testing may reduce some of the screening barriers faced by medically underserved women [16]. Consistent with HPV self-collection studies conducted in other states [17–21] and countries [22–29], our two previous studies in North Carolina demonstrated high acceptability of mailed self-collection samples for HPV testing among low-income women overdue for cervical cancer screening (e.g., 96–98% of participants reported being willing to perform HPV self-collection in the future) [30, 31].

Behavioral theory and empirical evidence indicate that lower levels of perceived barriers and higher levels of perceived risk of developing cancer are associated with higher rates of screening completion [32–37]. Several studies in Europe and Canada have found that mailing at-home HPV self-collection kits to women who have not responded to previous cervical cancer screening reminders leads to higher screening completion [15]. For example, in the Netherlands, 31% of under-screened women randomized to self-collection completed screening, compared to only 7% of those who were sent reminders to attend screening in clinic [38]. These studies also identified high rates of follow up to in-clinic Pap testing (up to 95%) among women receiving HPV-positive self-collection results [38, 39] and that use of HPV self-collection at home led to greater detection of CIN2+ than either screening reminders or scheduling assistance [38, 40–42]. These studies were conducted in countries with national screening registries, screening reminder systems, and universal health care, creating a different healthcare landscape than in the USA. To our knowledge, the US studies published to date that have assessed screening completion from HPV self-collection have used self-collection as their primary endpoint, independent of follow up to screening in clinic among self-test, HPV-positive women [17, 43].

### Objectives

In this RCT we will determine whether offering at-home self-collection of samples for HPV testing (followed by assistance scheduling screening in clinic for those with a positive HPV self-test result) increases the completion of cervical cancer screening among under-screened women compared to offering clinic scheduling assistance alone. We also will examine possible mechanisms explaining the effect or lack of effect of the intervention and will estimate the incremental cost per woman screened of offering self-collection of samples at home for HPV testing, with scheduling assistance, compared to clinic scheduling assistance alone. We hypothesize that offering HPV testing by mailing samples self-collected at home will result in greater screening completion, due to an increase in participants’ perceived risk of developing cancer.

## Methods/design

### Overview

We will conduct an open-label, parallel-group RCT of the impact of mailing self-collection samples for HPV testing on cervical cancer screening among women who are rarely or never screened.

### Participants and setting

Participants will include a minimum of 510 women in North Carolina who are overdue for cervical cancer screening (“under-screened”), defined as not having a Pap test in the past 4 years and without HPV testing in the past 6 years. Our definition of being overdue for screening is based on the American College of Obstetricians and Gynecologists screening guidelines, which recommend that women who have a Pap/HPV co-test be screened every 5 years and women who have only a Pap test be screened every 3 years [44]. Since the USA does not have a national screening registry, we will rely on participant self-report to identify women overdue for cervical cancer screening. Participants will be between the ages of 25 and 64 years, as HPV testing has been approved by the Food and Drug Administration (FDA) for primary screening of women age 25 years or older, and uninsured women up to age 64 years may be covered by Medicaid or the North Carolina Breast and Cervical Cancer Control Program (NC BCCCP) [3]. Participants must be non-pregnant, with an intact cervix (no history of hysterectomy), with income ≤ 250% of the US FPL, uninsured or enrolled in Medicaid, and living within the catchment area of a study-associated clinic. Income, insurance, and study eligibility criteria ensure that participating women will be eligible to receive free or low-cost screening and follow-up care through Medicaid or NC BCCCP.

We will recruit participants from 21 counties in North Carolina over an estimated 36 months. Study clinics will be located in 12 of these counties: Bertie, Camden, Chowan, Cumberland, Currituck, Gates, Guilford, Mecklenburg, Pasquotank, Perquimans, Sampson, and Wake. Participants will be recruited through multiple avenues. The primary mode of recruitment will be advertising through printed materials (flyers, posters, roadside signs, door hangers, buses, and newspapers), online (primarily on Craigslist.org), and radio. We will develop comprehensive lists of local agencies and community organizations providing services to low-income women in the target counties and collaborating with these groups to disseminate information about the study to their clients. Study outreach workers will also recruit participants directly at community events and through community organizations.

### Eligibility screening, consent, and enrollment

Women who call the MBMT-3 study phone number, a toll-free study hotline run by the American Sexual Health Association (ASHA), will reach a staff member who will screen callers for eligibility. Additionally, the study website will have a short online eligibility questionnaire; study staff will review the information and follow up on potentially eligible women. Women recruited in person by study staff will also complete eligibility screening verbally at that time.

At enrollment, we will collect contact information (e.g., phone numbers, best call times, mailing addresses, email, and an alternate contact if the participant cannot be reached directly) to provide multiple options for follow up. Eligible women will receive informed consent forms by mail, along with Health Insurance Portability and Accountability Act (HIPAA) authorization forms to obtain screening results and treatment outcomes from collaborating clinics and outside providers, if needed.

### Randomization and blinding

When the study receives eligible women’s completed consent forms, they will be enrolled into the study and randomized to the intervention or control arm. Randomization will be by permuted block design using blocks of 9 (due to the planned 2:1 ratio for the ratio of intervention to control) [45], stratified by county, using the randomization function of the web programming language hypertext processor (PHP) [46]. We will have a larger intervention group to support analyses of the responses of women with self-collection HPV-positive results. Neither study participants nor study staff will be blinded to the assigned arm. Interviewers will be blinded to study arm for the portion of the post-intervention survey that assesses perceived risk and related psychosocial measures.

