### Trial status

The trial was registered on ClinicalTrials.gov on 11 January 2016 as protocol NCT02651883. Recruitment began in April 2016, is currently ongoing, and will continue at least through December 2019.

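### A single block size of 9 within county, published while this open-label trial is still recruiting, makes about 17–21% of allocations predictable to anyone who can see a county's allocation sequence

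*Protocol article*

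**What the plan says.** All statements are in the protocol article.

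- **Overview:** "We will conduct an open-label, parallel-group RCT".
- **Randomization and blinding:** "Randomization will be by permuted block design using blocks of 9", and the reason given is "due to the planned 2:1 ratio for the ratio of intervention to control". Allocation is stratified by county and made by a PHP function once a woman's completed consent form has been received. No second block size and no random variation of size is mentioned. On masking: "Neither study participants nor study staff will be blinded to the assigned arm". The one exception is that interviewers are blinded for the part of the post-intervention survey on perceived risk and related measures.
- **Participants and setting:** "We will recruit participants from 21 counties in North Carolina over an estimated 36 months". Study clinics are in 12 of these counties. Overdue status rests on self-report.
- **Eligibility screening, consent, and enrollment:** staff screen women by hotline, by website follow-up or in person. Consent forms then go out by mail.
- **Trial status:** "Recruitment began in April 2016, is currently ongoing, and will continue at least through December 2019".

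**The concern.** With one known block size, the end of each block within a county can be worked out from what came before. An open-label design removes the usual obstacle to doing so, because the arms of earlier women are not hidden by masking. Publishing the size during recruitment removes another. The stated reason does not require this choice: 2:1 needs a block size divisible by 3, not the single value 9.

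What is at stake is freedom from selection at entry. The primary outcome is behavioural: a negative result on a returned kit, or clinic attendance. A woman's motivation plausibly drives both. If the order in which women enter a county's sequence could be influenced with the next arm known, motivation could differ between arms for reasons other than chance.

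**Working it through.** **Inputs.** Block of 9 at 2:1, hence 6 intervention and 3 control (Randomization and blinding). 510 women (Power calculations). 21 counties, 12 with study clinics (Participants and setting). Enrolment by county is not given, so even spreads are assumed and a range is shown.

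**The plan's own figure.** The article gives no predictability figure. Its power statement is 88–94% for 340 v 170 and a 15-point difference. With an assumed two-sided 5% level and a continuity correction, I obtain 87.7% (60% v 45%) to 93.9% (80% v 65%). It reproduces, and this point does not affect it.

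**Certain places in a full block.** There are C(9,3) = 84 equally likely orderings. A place is certain when only one arm remains in the block. The number of orderings in which each place is certain is:

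| Place | Orderings of 84 | Share |
|---|---|---|
| 1–3 | 0 | 0% |
| 4 | 1 | 1.2% |
| 5 | 4 | 4.8% |
| 6 | 10 | 11.9% |
| 7 | 21 | 25% |
| 8 | 42 | 50% |
| 9 | 84 | 100% |

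The sum is 162/84 = 1.93 of 9 = 21.4%. The closed form agrees: 6/(3+1) + 3/(6+1) = 1.50 + 0.43 = 1.93. So 1.50/1.93 = 78% of the certain places are intervention.

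**Across the trial.**

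- All blocks full: 510 × 0.214 = about 109 women. This is an upper figure.
- 12 counties, even spread: six of 42 women and six of 43. Each has 4 full blocks plus 6 or 7 places, so 663/84 = 7.89 or 684/84 = 8.14 certain places. Total 6 × 7.89 + 6 × 8.14 = 96.2, or 18.9%.
- 21 counties, even spread: fifteen of 24 women and six of 25. Each has 2 full blocks plus 6 or 7 places, so 339/84 = 4.04 or 360/84 = 4.29. Total 15 × 4.04 + 6 × 4.29 = 86.25, or 16.9%.
- Uneven county sizes (simulated): averages of 18.6–19.5%.

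The range is therefore about 17–21%. In the 21-county case, certain control places number about 42 full blocks × 0.43 = 18 women.

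**Guessing.** Naming the commoner remaining arm is right 72.8% of the time in full blocks, against 66.7% from the 2:1 ratio alone.

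**Effect of varying the size.** These are simulated strata of 24 women, with an observer who knows the set of sizes and the stratum's history. Results vary by a few tenths of a point between runs.

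| Sizes | Certain in advance | Best guess right |
|---|---|---|
| 9 only | about 17% | about 71.5% |
| 3, 6, 9 | about 3.5% | about 73.5% |
| 6, 9, 12 | about 2.2% | about 71.4% |

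Both sets nearly remove certainty, but including 3 makes guessing slightly easier than with 9 alone. Sizes 6, 9 and 12 avoid that. The gain lies in certainty; the guessing rate hardly moves.

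**The case against.** The case against has four parts.

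1. **Access.** A reader might infer that unblinded staff do know a fifth of the allocations in advance. The article does not support that. It says staff are not masked to arm; it does not say that anyone who screens, recruits or enters consents sees a county's full ordered list. Who has access, and how the sequence is concealed, may be in the full protocol, and their absence from an article is no fault. This stands, and the figure has to be read as conditional on access.

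2. **Opportunity.** Consent forms go out and come back by mail before a program allocates. At eligibility screening a woman's place in the sequence is not yet fixed, because it depends on which forms return first. This also stands. It leaves mainly the timing or order of entering returned forms, and the article does not suggest that this is manipulated.

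3. **Size.** Most certain places go to intervention, already the two-in-three favourite, and correct guessing rises only from about 67% to 73%. True, which is why the point is minor.

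4. **Adjustment.** A reader might infer that no adjustment could recover selection on motivation. That is too absolute. Worry, perceived barriers and self-efficacy are measured at baseline (Table 1), and the analytic section provides for adjusting for covariates associated with both arm and completion. These measures are at best proxies for motivation, so the protection is partial.

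What remains is that the block size is stated, its stated reason does not require it, and it was published during recruitment. The article commits itself to this choice, so it is not a detail left to another document.

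**Conclusion.** The point holds as a minor, avoidable weakness in the design. A person able to see a county's past allocations in order could know about 17–21% of allocations beforehand: 21.4% in full blocks, and about 17% if 510 women are spread evenly over 21 counties. Roughly four in five of these are to intervention.

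The figure rests on three assumptions: block size 9 throughout, the observer knows that size, and the observer tracks the full sequence within county. The first two follow from the article; the third is not stated there. It is a measure of predictability, and nothing in the document shows that allocations were foreseen or acted on, or that the estimated difference in screening completion is biased. The ratio, strata, power and analysis are not called into question.

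**What to change.** For women still to be randomized, let each county's current block run to its end. Then draw each later block size at random from a set of multiples of 3 such as 6, 9 and 12, leaving out 3. Keep the sizes and the county sequence from staff who screen, recruit or enter consents. In Randomization and blinding, say that block sizes vary at random within county and who is kept from the sequence, without listing the sizes until recruitment ends. If the sequence is already hidden from these staff, a sentence saying so would answer most of the concern.

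The cost is a small change to the randomization program. It cannot help women already allocated since April 2016. Blocks of 12 may leave slightly more imbalance in small counties. The 2:1 ratio, the stratification and the analysis stay as they are.

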### Intervention and control procedures

Women assigned to the intervention arm will receive an HPV self-collection kit by mail, which will include an informational sheet, instructions, and materials to self-collect a cervico-vaginal sample, and a pre-paid envelope to return it by mail (Fig. 1). When HPV self-collection test results are available, ASHA staff will call the participant to deliver her HPV results and schedule her for a free appointment in clinic regardless of the result. Women who with self-collection HPV-positive results will be informed that their results indicate a higher risk for cervical cancer and will be advised to schedule an appointment to complete Pap/HPV co-testing at a study clinic (see results delivery scripts, Additional file 1: Appendix 1). Women with self-collection HPV-negative results will be told that their results indicate lower risk for cervical cancer, but that doctors cannot use self-collection results to make decisions about their care. Participants with both HPV-negative and HPV-positive self-collection results will be able to schedule an appointment for free screening in clinic during the HPV results delivery call. Participants whose self-collection results are inconclusive will be contacted and given the option to try the self-collection again or schedule a clinic appointment. A participant who has not returned a self-collected sample within 3 weeks will receive a mailed reminder letter to return the kit. If the kit still has not been returned 2 weeks later, she will receive a reminder call, at which point she will receive assistance to schedule a clinic appointment if she prefers.

**Fig. 1 Fig1:**
[figure not shown]
MBMT study flow. ASHA, American Sexual Health Association; HPV, Human papillomavirus; HIPAA, Health Insurance Portability and Accountability Act

Control-arm participants will receive scheduling assistance 1 week after enrollment. This scheduling assistance call provides brief education on cervical cancer and screening, followed by the opportunity to schedule a free screening appointment in clinic for Pap/HPV co-testing. Education will emphasize that cervical cancer is preventable with regular screening and early treatment; the participant is due for screening based on doctor recommendations; and the participant is eligible for free screening at a local clinic. Participants will be directed to go to a study-associated clinic based on residence.

Up to three call attempts will be made to contact a participant to deliver her self-test results or to assist with scheduling a clinic appointment. If these call attempts fail, the study will send a final letter inviting the participant to call the study hotline to receive her HPV self-test results. Participants with HPV self-test positive results who are not reached by phone will receive a letter with their results, strongly recommending screening in clinic.

### Sample collection and laboratory testing procedures

The self-collection kit will contain a brush and vial of sample preservation solution, simple illustrated instructions, the study hotline to call with questions, and a pre-addressed, pre-paid mailer for sample return. An information sheet will also be included in the kit to provide education about HPV, cervical cancer, and screening by clinic and self-collection methods. As in previous studies [42, 47–49], sample self-collection will be performed using a Viba brush (Rovers Medical Devices, B.V., The Netherlands), which the participant will insert into the vagina as far as the brush can comfortably go, and she will rotate it five times and then remove it. The participant will then separate the brush head from the handle using a small brush remover tube and place it into a collection tube containing 4.3 mL of Aptima sample transport medium (Hologic, Inc., San Diego, CA, USA). The sample transport medium is non-toxic, approved for mailing via the US Postal Service and validated to keep specimens stable for HPV RNA testing for at least 60 days at room temperature. We developed the educational materials, scripts, and illustrated instructions for completing self-collection in English and Spanish for low-literacy populations using National Institutes of Health (NIH) plain language guidelines [50] and based on pilot-testing the materials with women in the target population. Participants who attend an appointment at a study clinic will receive a pelvic exam by a clinical professional to collect a cervical sample using an endocervical brush and spatula, which the clinician will place immediately into PreservCyt media (Hologic, Inc.).

Samples self-collected at home will be sent to study staff and then for testing at the Laboratory Corporation of America laboratory in Burlington, North Carolina. Clinician-collected samples will be sent directly to the laboratory for testing. The laboratory will perform HPV testing on self-collected and clinician-collected samples using the Aptima HPV assay (Hologic, Inc.), an FDA-approved molecular amplification assay that qualitatively detects E6/E7 mRNA of 14 HPV genotypes (16, 18, 31, 33, 35, 39, 45, 51, 52, 56, 58, 59, 66, and 68), according to the manufacturer’s instructions [51]. For samples testing positive for the high-risk HPV panel, the laboratory will test for HPV types 16 and 18/45 using the FDA-approved Aptima 16 18/45 assay. All Aptima assays and instrument systems are FDA-approved for testing clinician-collected specimens. Though HPV testing on samples self-collected at home is not FDA-approved for any assay, studies have validated the Aptima HPV assay for self-collection [47, 48, 52–54]. To determine co-infection with other sexually transmitted infections, self-collected and clinician-collected samples will be also tested for *Chlamydia trachomatis* and *Nesseiria gonorrheae* using the Aptima Combo2 assay and for *Trichomonas vaginalis* using the Aptima TV assay (all Hologic, Inc.). A trained operator at the laboratory will perform these tests on the fully automated Panther system, according to the manufacturer’s instructions; clinician-collected samples will be also analyzed for liquid-based cytology using the ThinPrep 2000 Processor (Hologic, Inc.) and classified according to the 2001 Bethesda System at the Labcorp laboratory. If any cytological cervical abnormality (i.e., atypical squamous cells of undetermined significance or worse), HPV, or sexually transmitted infection is identified in a clinician-collected cervical sample, the clinician will refer the participant for follow-up diagnostics and treatment per standard-of-care [55].

